## Statistical methods

### Statistical methods for primary and secondary outcomes {20a}

Statistical analyses will firstly be performed using descriptive analysis to characterize the distribution of the events studied. Categorical variables will be investigated using simple absolute frequencies. Continuous variables will be investigated by measures of central tendency and dispersion. Parametric or non-parametric tests will be used considering the distribution nature of the variables studied. A significance level of 5% will be adopted for all statistical tests. Tests to verify variable behavior and comparisons of proportions analyses, such as the application of the chi-square test or Fisher’s exact test, will be discussed later with a qualified statistician. Tests for comparison of means between groups, analysis of correlations between continuous variables and logistic regression analysis, will also be discussed with the statistician. Data will be tabulated and analyzed using the R Project for Statistical Computing software (R-3.2.4 for Windows).

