### Outcomes {12}

#### Primary outcome

The primary outcome will be the assessment of NAFLD resolution, or change in its grade, as assessed by the difference in the attenuation coefficient between liver and spleen, obtained by CT of the upper abdomen, at the end (after) compared to beginning (before) the trial. In summary, the primary outcome is to investigate whether silymarin supplementation can reduce liver fat content in NAFLD patients, measured by a CT scan.

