#### Secondary outcomes

The secondary outcomes investigated in this trial include:Differences in ALT, AST, γGT, and AP levels after *versus* before;Difference in ferritin levels after *versus* before;Difference in fasting glucose, insulin, HbA1C, and HOMA-IR levels after *versus* before; andDifference in BMI and WC after *versus* before.

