### Sample Size {14}

The sample size was determined through an accuracy analysis of the primary outcome. A significance level of 0.05 and a power of 80% were adopted, which resulted in a minimum sample size of approximately 132 participants.

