#### Allocation consultation

At this appointment, participants receive their CT scan and blood test results and are submitted to a second anthropometric assessment. At this consultation, a new form with nutritional and dietary data is completed by the researcher, and patients are given additional nutritional guidelines to complement the advice offered in the screening appointment. Subsequently, participants are sent to the clinical research pharmacy of the Hospital Complex for capsule collection according to their randomization.

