## Trial status

Patient recruitment started in February 2019 and ended in May 2022. A significant delay in study progression and data collection was attributed to the SARS-CoV-2 pandemic and subsequent lockdowns.

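### The test is to be chosen from the observed distribution and was still open after recruitment ended, and no baseline-adjusted between-group model is named

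*Protocol article*

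**What the plan says.** The section on statistical methods for primary and secondary outcomes {20a} starts with description of the data and then gives its rule: "Parametric or non-parametric tests will be used considering the distribution nature of the variables studied". Tests for proportions (chi-square or Fisher) are put off to a later discussion with a statistician. For the rest it says: "Tests for comparison of means between groups, analysis of correlations between continuous variables and logistic regression analysis, will also be discussed with the statistician". It also states: "A significance level of 5% will be adopted for all statistical tests". No model, covariate or effect measure is named for any outcome.

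The primary outcome is resolution or change of grade, judged from the liver-spleen attenuation difference on CT "at the end (after) compared to beginning (before) the trial". The same section then restates it as a reduction in liver fat content measured by CT. The secondary outcomes take the same form, for example "Differences in ALT, AST, γGT, and AP levels after" versus before. The abstract and Table 1 place CT and blood tests at the start and end of the study, so every completer should have a baseline value.

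On timing, the trial status section says: "Patient recruitment started in February 2019 and ended in May 2022". The article appeared in March 2023 with the tests still undecided.

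**The concern.** Three features combine.

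- The stated rule lets the data select the test.
- The selection was still to be made when all participants had been recruited.
- The primary outcome can be read on more than one scale (resolution, grade change, continuous attenuation difference), so the form of the outcome is open as well as the test.

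Whoever chooses late, with outcome data at hand, could pick among several defensible analyses, and the nominal 5% then no longer describes the procedure.

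Separately, subtracting the baseline is not the same as adjusting for it. A change score forces a slope of 1 on the baseline. Where the true slope is smaller, the change score is noisier than it needs to be and leaves chance baseline differences between the arms incompletely corrected. The values needed to do better are already collected.

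**Working it through.** **Inputs from the article.** The sample size section gives: "A significance level of 0.05 and a power of 80% were adopted, which resulted in a minimum sample size of approximately 132 participants". The 5% level applies to all tests ({20a}).

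**Assumptions.** Allocation 1:1 (66 per arm), two-sided tests, equal SD at both time points, and a baseline-outcome correlation rho between 0.3 and 0.9. The article states none of these.

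**The plan's own figure.** N = 132 cannot be reproduced, because the article gives no effect size, SD or rates. It can only be solved backwards: d = (1.960 + 0.842) × √(2/66) = 0.488 SD. This serves below as a reference effect and is not a figure of the plan.

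**Step 1: the distribution switch alone.** Null trials, 66 per arm, 8,000 runs per scenario. Shapiro-Wilk is run in each arm, followed by the t-test if neither rejects and by Mann-Whitney otherwise.

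| Distribution | Switching rule | Smaller p of the two tests |
|---|---|---|
| Normal | 5.3% | 6.2% |
| Gamma | 4.6% | 6.4% |
| Lognormal | 4.9% | 7.5% |

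Monte Carlo error near 5% is √(0.05 × 0.95/8000) = 0.24 points. The switch, applied mechanically, is harmless. Choosing the more favourable test costs 1 to 2.5 points.

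**Step 2: test, scale and outcome form all open.** The same set-up, with normal data, taking the smallest p among five analyses: t-test on end values, t-test on change, ANCOVA, Mann-Whitney on change, and chi-square on a dichotomised change.

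| rho (assumed) | Best of five | One fixed ANCOVA |
|---|---|---|
| 0.5 | 12.9% | 5.0% |
| 0.7 | 13.5% | 5.1% |
| 0.9 | 13.2% | 5.0% |

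**Step 3: precision.** Relative to the variance of end values, the change score has 2(1 − rho) and ANCOVA has 1 − rho². Their ratio is (1 − rho²) / [2(1 − rho)] = (1 + rho)/2. If 132 gives 80% power for a change score:

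| rho (assumed) | ANCOVA / change variance | N for 80% with ANCOVA | ANCOVA power at 132 |
|---|---|---|---|
| 0.3 | 0.65 | 86 | 93.5% |
| 0.5 | 0.75 | 100 | 89.9% |
| 0.7 | 0.85 | 114 | 86.0% |
| 0.9 | 0.95 | 126 | 82.0% |

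The saving over a change score is thus 132 − 100 = 32 participants at rho 0.5, and 132 − 126 = 6 at rho 0.9.

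The gain shrinks if the baseline CT, which is also the entry test, narrows the baseline spread. With the baseline truncated at an entry cut-off (population mean assumed 0.6 SD beyond it, 3,000 runs), power for ANCOVA versus change was 0.80 versus 0.75 at rho 0.6, 0.79 versus 0.77 at 0.7, and 0.79 versus 0.77 at 0.8. That is a loss of 2 to 5 points.

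**The case against.** The strongest reply has four parts.

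**The baseline is used.** Every outcome is an after-minus-before difference. A reader might infer that the baseline is ignored and compare ANCOVA with an analysis of end values, where the power gap is wide (0.52 to 0.69 against about 0.80 in the truncated set-up). The article does not support that comparator, since its outcomes are changes. What is absent is adjustment for baseline as a covariate.

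**The comparison is between arms.** Because both arms receive dietary advice ("patients are given additional nutritional guidelines to complement the advice offered in the screening appointment") and entry depends on the baseline CT, both may improve without any drug effect. A reader might infer that efficacy will be judged by before-after tests within an arm. In the truncated set-up such a test in the control arm rejects in 22 to 41% of null trials (rho 0.8 to 0.6). No section plans this test. The trial design section {8} sets a superiority framework against placebo, and {20a} names a comparison of means between groups. In the same set-up the between-arm test of change rejects in 4 to 5% of null trials. The 22 to 41% also depends on an invented cut-off: at rho 0.7, moving the assumed mean from 0.6 to 1.0 or 1.5 SD beyond it lowers the figure from about 33% to 14% or 6%.

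**The switching rule is nearly harmless.** Step 1 confirms this.

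**A separate analysis plan may fix the model.** Covariates, transformations and robust errors are ordinary content for such a plan, and the implementation section {16c} keeps the envelopes closed to the principal investigator until the last participant completes.

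The first three stand and limit the claim. The fourth stands only in part. The point rests on what {20a} affirmatively states, a data-led choice made later, and a plan that fixed one model in advance would replace that rule. The envelopes are also not the only safeguard to consider: the unblinding section {17b} gives the statistician access to allocation, and the article does not say whether this is the statistician who will advise on the tests.

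**Conclusion.** The point holds in a limited form. The article states a test choice that depends on the data and was still deferred after recruitment ended, and it names no baseline-adjusted between-group model.

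- **Type I error.** The risk comes from leaving test, scale and outcome form open together. About 13% is what results if the most favourable of five analyses is reported. It is an upper illustration of the freedom left, not a prediction of what the investigators will do.
- **Precision.** ANCOVA removes between 5% (rho 0.9) and 25% (rho 0.5) of the change-score variance, and less if entry selection narrows the baseline. Rho is assumed throughout.

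The documents do not support saying that the baseline is discarded, that the distribution switch itself inflates error, or that efficacy claims will rest on within-arm tests.

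**What to change.** Before the allocation envelopes are opened, replace the rule in {20a} with a fixed analysis. If they have already been opened, say so and date the plan.

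1. **Primary scale.** Name the continuous liver-minus-spleen attenuation difference, which agrees with the article's own summary of the primary outcome. If grade or resolution is kept as primary, use an ordinal or logistic model adjusted for baseline attenuation, because linear ANCOVA does not fit those outcomes.
2. **Primary model.** For the continuous scale, ANCOVA of the end-of-treatment value on arm and baseline value, reporting the adjusted mean difference with 95% CI at two-sided 5%.
3. **Secondary outcomes.** The same model, each with its own baseline. Log-transform markers expected to be skewed (such as transaminases, γGT, AP, ferritin, insulin and HOMA-IR), listed in advance and reported as geometric mean ratios.
4. **Sensitivity.** Robust or bootstrap standard errors and a non-parametric analysis as checks, not as substitutes selected after looking at the data.
5. **Basis of claims.** State that efficacy conclusions rest on the between-arm comparison.

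The cost is wording only. The baseline measurements are already part of the schedule, and no change to sample size or conduct is needed.

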### Interim analyses {21b}

This is a low-risk intervention, as silymarin at the dosage adopted in this trial has been considered safe and well-tolerated. All patients were carefully followed up in person and by telephone, aiming to identify any adverse event. Only patients who successfully complete the trial will have their data included in the final data analyses.

### Methods for additional analyses (e.g., subgroup analyses) {20b}

No additional analysis will be performed.

### Plans to give access to the full protocol, participant-level data, and statistical code {31c}

The full protocol, participant-level data, and statistical code generated in this trial will be available from the corresponding author in electronic format on reasonable request. Identifiable information such as full name, address, and date of birth will not be shared for confidentiality purposes.

## Oversight and monitoring

### Composition of the coordinating center and trial steering committee {5d}

The PI as a blind evaluator and a coordinator assistant will coordinate all phases of the study, the randomization, and record-keeping of I and C participants. Patient and Public Involvement Groups (PPIG) were not involved in the design, recruitment, or execution of this trial, nor will they be involved in the reporting and dissemination of this research trial, with the exception of dissemination through their own social media channels if they wish.

### Composition of the data monitoring committee, its role and reporting structure {21a}

There will be no data monitoring committee since only the primary evaluator, the research team, and the coordinator assistant will have access to the clinical trial data. Additionally, this trial is a low-risk intervention, and participants are advised to report any unexpected or adverse effects to the research team.

### Adverse event reporting and harms {22}

The capsules provided to patients in both groups were produced and kindly donated by Singular Pharma (Salvador BA, Brazil). Singular Pharma have contractually undertaken not to interfere in any stage of the trial and have allowed the dissemination of any trial results, even if such results do not confirm the hypothesis that silymarin may be a beneficial adjuvant compound for the treatment or management of NAFLD. The donation document was submitted to, and approved by, the Ethics Committee.

Silymarin is commonly prescribed by clinicians and nutritionists and its use is considered safe [15]. According to data available from studies included in a previously published meta-analysis [15], there have been no reports of serious adverse events categorized as frequent or uncommon. However, a few studies have reported episodes of nausea, vomiting, and abdominal discomfort as rare adverse events [16, 17, 20]. Interestingly, a few clinical trials and meta-analyses that have investigated the effects of supplements containing silymarin did not record adverse events or complications associated with supplementation, suggesting good tolerability and safety to participants [16, 17, 20].

In the current trial, participants were advised to immediately stop taking the capsules and contact the research team as soon as possible in the event of any unexpected or adverse effect, or any discomfort supposedly associated with the capsule intake. All participants were followed up and monitored every 4 weeks at the NHOC, where the data collection and weekly telephone follow-up calls took place. All possible adverse events or complications observed were recorded, evaluated, and reported in the study.

### Frequency and plans for auditing trial conduct {23}

Fortnightly meetings were held with the group of researchers involved in the study to discuss development and question clarification. An independent researcher external to the research team will verify the data collected during the study. If any documents are missing or information is inconsistent, the Ethics Committee will be notified. Lastly, if there is any change in the study, the ethics committee, the journal, and *ClinicalTrials* will be notified immediately.

### Plans for communicating important protocol amendments to relevant parties (e.g., trial participants, ethical committees) {25}

This study has been approved by the Research Ethics Committee of the [name] University Hospital Complex under application protocol 2.635.954. The research must be undertaken as set out in the approved documents for the approval to be valid. The Research Ethics Committee will be contacted should the research team intend to make any amendments to the approved research.

Patients eligible to join the trial were invited to sign the consent form after receiving all the information regarding the trial, including potential risks, and after having their questions answered in full. The consent form was developed in compliance with guidelines and regulatory standards for research involving human beings. During all stages of this trial the standards set out in the Brazilian Resolutions 196 and 466/2012, approved by the National Health Council, were followed. The Good Clinical Practices of the Document of the Americas of 2008 were also followed.

All participant information is kept confidential. At the end of the trial, all participants were advised to maintain their clinical and nutritional follow-up appointments at the NHOC of the University Hospital Complex according to their health needs.

### Dissemination plans {31a}

The results of this randomized controlled clinical trial are expected to be disseminated through presentations at conferences and publications in peer-reviewed journals.

## Discussion

This clinical trial aims to assess the efficacy of silymarin in adult patients diagnosed with NAFLD. The prevalence and incidence of NAFLD are expanding at an accelerated pace and currently pose a burden to public health systems. There are currently limited pharmacotherapeutical options for NAFLD [3, 4].

Silymarin has been hypothesized as a useful adjuvant therapeutic resource in clinical practice for NAFLD therapies, as beneficial hepatoprotective properties attributed to silymarin have been reported [21]. A few clinical studies have observed improvement in liver function and injury biomarkers after silymarin supplementation in various liver diseases [14, 22–25]. Liver biomarker levels are a true representation of the progression of liver disease and their levels are strongly associated with greater morbidity. Amelioration of liver biomarkers attributed to silymarin therapy is of great benefit for sufferers and a promising tool worth of further investigation .

Several studies investigating the effects of silymarin in patients with liver diseases unfortunately feature some methodological biases. A meta-analysis of clinical trials published by our research team [15] found a high degree of heterogeneity and low methodological quality in the qualitative assessment of the clinical trials included in the meta-analysis. Lastly, only very few published studies recruiting reasonable sample sizes have evaluated the efficacy of silymarin supplemented as a single test item in adult patients with NAFLD; we have addressed such a problem in our study by supplementing silymarin only.

The lack of robust evidence, as well as inconsistencies identified in existing publications, reinforce the need for additional clinical trials with stronger methodological designs to further elucidate the roles of silymarin, if any, in the treatment and management of NAFLD. The results of the present clinical trial may contribute to the dissemination of reliable outcomes that may or may not support the recommendation of silymarin adjuvant therapy for NAFLD patients.

## Trial status

Patient recruitment started in February 2019 and ended in May 2022. A significant delay in study progression and data collection was attributed to the SARS-CoV-2 pandemic and subsequent lockdowns.

## Data Availability

Any data required to support the protocol can be supplied on request.

## Abbreviations

NAFLD: Non-alcoholic fatty liver disease
T: Test
C: Control
MS: Metabolic syndrome
T2D: Type 2 diabetes
IR: Insulin resistance
NASH: Non-alcoholic steatohepatitis
ALT: Alanine aminotransferase
AST: Aspartate aminotransferase
γGT: Gamma-glutamyl transferase
AP: Alkaline phosphatase
BMI: Body mass index
WC: Waist circumference
CONSORT: Consolidated Standards of Reporting Trials
SPIRIT: Standard Protocol Items- Recommendations for Interventional Trails
HIV: Human immunodeficiency vírus
IC: Informed consent
